## Abstract

**Background:**

Suicide is a major public health issue worldwide. Those who have made a recent suicide attempt are at high risk for dying by suicide in the future, particularly during the period immediately following departure from a hospital emergency department. As such the transition from hospital-based care to the community is an important area of focus in the attempt to reduce suicide rates. There is a need for evaluation studies to test the effectiveness of interventions directed to this stage (termed ‘aftercare’ interventions).

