### Study sample

Participants in the Aftercare intervention will be drawn from people who attend one of the three participating emergency departments as a result of a suicide attempt or high risk for suicide, who meet the referral inclusion criteria. Participants’ risk for suicide (and therefore suitability for the Aftercare intervention) will be determined by the hospital staff using standard mental health assessment protocols. Those considered for referral to the Aftercare intervention will be 16 years of age and over. Those excluded from consideration for the service will be admitted to the hospital as an inpatient, or being actively case managed by mental health services, at that time of presentation to the emergency department. Those who consent to participate in the Aftercare intervention and who consent for their data to be included in the study will form the intervention group for the study.

The control group (TAU) will be sourced via de-identified hospital data extraction. They will be people 16 years of age and over who attend a participating emergency department as a result of a suicide attempt or high risk for suicide but either do not receive, or do not accept, a referral to the Aftercare intervention (i.e. did not wish to participate in the service; were unable to participate for other reasons e.g., time commitments; or had not received a referral to the service e.g. standard procedures were not followed in the emergency department). Pre-determined hospital codes for suicide attempt or high risk for suicide will identify controls. They will be selected by identifying those patients who presented to any of the emergency departments in the study during the study period, and identifying those who presented in the same month, who met the study inclusion criteria, and who had the closest emergency department presentation dates to the participants undertaking the Aftercare intervention and enrolled in the trial*.* A human research ethics waiver for consent was granted; all data is sourced via hospital data and code sets.

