### Study procedure

Health consumers attending their local emergency department following a suicide attempt or at high risk for suicide are provided with a mental health assessment by clinical staff, where risk for suicide (and therefore suitability for the Aftercare intervention) is determined by standard hospital mental health assessment protocols. Staff determine whether the consumer warrants admission to hospital, as per the NSW Ministry of Health policies. If the consumer is not admitted to hospital as an inpatient, standard procedures include one follow-up phone call or home visit by the local health district’s mental health outreach team within seven days and a discharge letter to the person’s general practitioner. If the consumer is eligible for referral to the Aftercare service he/she will also be given a brief overview of the service by an emergency department clinician and at that time may choose to provide verbal consent to be referred to the service. The emergency department staff will contact the Aftercare service by phone and provide a referral. The participant flow process is shown in Fig. 1.

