#### Aftercare intervention

The Aftercare service is administered through a collaboration of three community-based organisations in the region; Grand Pacific Health, Flourish Australia and the South Coast Medical Service Aboriginal Corporation. Referrals are taken by Grand Pacific Health and allocated according to location.

The consumer will be contacted by an Aftercare peer worker within one hour of the referral being received from the emergency department, while the consumer is still in the emergency department; or if the referral is made outside of operational hours they will be contacted the following day. A brief overview of the Aftercare program will be provided and, with consent, an initial community-based appointment with an Aftercare mental health clinician will be scheduled for the following day, or otherwise, as best convenient for the participant within the shortest possible timeframe.

Participants of the Aftercare service will attend the community-based service for their first appointment. Prior to their appointment, they will be provided with the research participant information sheet and consent form, and will have the opportunity to discuss the research further. Following this, they will complete the pre-intervention measures via tablet computer (or using pen and paper when appropriate).

The initial appointment with a mental health clinician will involve a collaborative assessment and planning session and take approximately one hour. The assigned peer worker will also be present and, with the consent of the participant, the participant’s family/carer will be encouraged to attend. Participants will complete the Suicide Status Form-4 (SSF-4) [53] with the mental health clinician. The SSF-4 is a multi-component clinical semi-structured assessment and treatment planning tool designed to assist in assessing the level of suicide risk and factors associated with suicidal thoughts. Six five-point Likert scales rate the degree of psychological pain, stress, agitation, self-hopelessness, self-hate, and overall suicide risk; and additional open-ended questions ask participants to elaborate upon these factors (e.g., “What I find most painful is…”). An earlier version of the form has demonstrated good convergent validity of these rating items with other established measures [55].

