### Data analysis

Analyses will be conducted using the Statistical Package for the Social Sciences version 25 [85] and SAS v9.4 [86]. Primary analyses will be conducted according to the intention-to-treat approach. Presentations to an emergency department with a repeat suicide-related event and for all-cause death will be compared between the two non-randomised groups (intervention vs control) using a Kaplan Meier plot where the initial presentation to an emergency department is designated as time zero, and using censoring. A log-rank test will compare the Kaplan Meier curves of the two groups.

A negative binomial regression model will be applied to the data to estimate the effect of the intervention on re-presentation rates, accounting for varying lengths of follow-up period and adjusting for service and person-level characteristics (e.g. facility, age, sex, indigenous status) and censoring.

To investigate the impact of the service on suicide risk factors (secondary outcome measures), a comparison of pre- and post-intervention outcome measures will be conducted for participants of the intervention using paired t-tests, or a Wilcoxon signed-ranks test (if the sample is non-normally distributed), adjusting for multiple comparisons (Bonferroni correction).

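### Follow-up starts at the emergency department visit, but intervention membership is settled only at later research consent; the resulting bias favours the intervention, is complete for deaths before consent and partial for re-presentations

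*Protocol article*

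**What the plan says.** All references are to the protocol article.

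- **Clock.** Data analysis: for the Kaplan-Meier plots of suicide-related re-presentation and all-cause death, "the initial presentation to an emergency department is designated as time zero". A log-rank test compares the curves. A negative binomial model handles re-presentation rates.
- **Membership.** Study sample, on who makes up the intervention arm: "Those who consent to participate in the Aftercare intervention and who consent for their data to be included in the study will form the intervention". Both consents are needed.
- **In the emergency department.** Study procedure: an eligible person "at that time may choose to provide verbal consent to be referred to the service". This is agreement to a referral, not entry to the study.
- **Research consent.** Aftercare intervention: "Prior to their appointment, they will be provided with the research participant information sheet and consent form". The appointment "will be scheduled for the following day, or otherwise, as best convenient for the participant within the shortest possible timeframe".
- **Controls.** Study sample: people who "either do not receive, or do not accept, a referral to the Aftercare intervention", taken from hospital data and chosen as those "who had the closest emergency department presentation dates to the participants undertaking the Aftercare intervention and enrolled in the trial". No condition requires a control to be alive or event-free on any later day.
- **Early risk.** The abstract describes the risk of dying by suicide as high, "particularly during the period immediately following departure from a hospital emergency department".

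**The concern.** Time zero comes before the act that defines one of the two groups. A participant has, by construction, lived from the emergency department visit to consent. A control has not had to. Any early death, and some early re-presentations, can therefore appear on the control curve but not on the intervention curve.

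This gap lies in the days the protocol itself treats as most dangerous. It can only lower the intervention group's apparent risk. All-cause death and re-presentation are both primary outcomes, and the log-rank test is unadjusted. The adjustment of the negative binomial model for facility, age, sex and indigenous status would not repair a misaligned start of follow-up.

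**Working it through.** **Inputs from the documents.** 12-month risk 16% (Sample size and statistical power), or 21.9% as the control figure of the Danish trial used there; 75 participants and 1265 controls; planned ratio .087/.219 = 0.397.

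**Assumed, because the documents do not give them.** The gap d from visit to consent (1 or 7 days), and the early event pattern: constant hazard over the year, or 10% or 20% of 12-month events in week 1, spread evenly within it. It is also assumed that any early event prevents entry.

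**The plan's own size.** A two-proportion calculation gives 75 per 1265 in two ways: .087 vs .219, two-sided with continuity correction; or .16 × 0.397 = .0636 vs .16, one-sided (power .805). The same two-proportion approximation is used below.

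**Formulae.** Let p be the control 12-month risk and E the risk before day d. For constant hazard, E = 1 − (1 − p)^(d/365). For share s in week 1, E = p × s × d/7. With no treatment effect, participants who must be event-free to day d have risk q = (p − E)/(1 − E), and the apparent risk ratio is q/p.

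The chance of a significant benefit in a two-sided .05 test is Φ[(p − q − 1.96·SE0)/SE1], where SE0 uses the pooled proportion and SE1 the separate ones, with 75 and 1265 people. Without bias it is 2.5%.

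**Example (7 days, 20% in week 1).** E = .16 × .20 = .032; q = .128/.968 = .1322; ratio .1322/.16 = 0.826. SE0 = .0434 and SE1 = .0404, so Φ[(.0278 − .0851)/.0404] is about 7.8%.

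**Results at p = 16%.**

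| Gap | Early pattern | E | q | Ratio | Events missing among 75 | False-benefit chance |
|---|---|---|---|---|---|---|
| 1 day | constant | .0005 | .1596 | 0.997 | 0.03 | 2.54% |
| 1 day | 10% in week 1 | .0023 | .1581 | 0.988 | 0.14 | 2.72% |
| 1 day | 20% in week 1 | .0046 | .1561 | 0.976 | 0.29 | 2.95% |
| 7 days | constant | .0033 | .1572 | 0.982 | 0.21 | 2.82% |
| 7 days | 10% in week 1 | .0160 | .1463 | 0.915 | 1.02 | 4.45% |
| 7 days | 20% in week 1 | .0320 | .1322 | 0.826 | 2.08 | 7.83% |

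At p = 21.9% and 7 days, the ratios run from 0.983 to 0.837 and the false-benefit chance from 2.9% to 9.6%.

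**If exclusion is only partial.** Suppose half of those with an early event still enrol. Then E is replaced by E/2. In the last row of the table, q = (.16 − .016)/(1 − .016) = .1463 and the ratio is 0.915 instead of 0.826. The tabulated ratios are thus the extreme for re-presentation under each set of assumptions.

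**Death.** Exclusion before consent is complete, but the documents give no all-cause mortality rate, so no size can be computed.

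**The case against.** The strongest reply has four parts.

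1. **Re-presentation time is not immortal.** The exclusions for inpatient admission and active case management apply at presentation, and nothing bars a person who re-presents and goes home from attending later. This stands. A reader might infer that every early event is removed from the intervention group on all primary outcomes. The documents support that only for death.
2. **The planned gap is a day, not a week.** This also stands, and on that plan the bias is small. But no maximum is stated, and the appointment may be set at the participant's convenience.
3. **The service begins in the emergency department.** Referral is accepted there, and a peer worker makes contact within an hour, or the next day if out of hours. This is true of the service, but study membership also needs research consent, which comes later. People who accept a referral but never attend, or never give research consent, fit neither group as defined.
4. **The analysis is by intention to treat, and the limitations admit self-selection.** Neither answers the point. Intention to treat protects when groups are fixed at time zero. The Limitations section concerns differences in motivation and outlook, not the start of follow-up.

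One further limit is that time zero is stated only for the Kaplan-Meier analysis. That the negative binomial person-time starts on the same day is a natural reading, not a stated rule.

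**Conclusion.** The misalignment is in the text, and its direction is certain: where it acts, it favours the intervention. It is complete for death before consent and partial for re-presentation.

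Its size depends on two quantities that the documents do not give, the delay and the share of early events. If an early event prevents entry, the null risk ratio is about 0.98 to 1.00 for next-day appointments and about 0.83 to 0.98 for delays of about a week.

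A reader might infer that this bias could produce the effect the trial is designed to find. It could not: the most extreme ratio computed is 0.826, against a planned 0.397. Nor can the mortality comparison be called badly distorted, since the expected number of deaths before consent is unknown and may be close to zero with next-day appointments. The case for correction is that the bias runs one way, touches the primary outcomes, and is cheap to remove.

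**What to change.** - Start each participant's follow-up at the research consent or first-appointment date. Give each date-matched control the same lag after its own emergency department visit.
- Apply identical landmark conditions to both groups. Everyone must be alive at the landmark. Then either require both groups to be event-free to that day, or in both groups count only events after it. The first option aligns the groups more fully. The second keeps more people but leaves some selection if those who re-present enrol less often.
- Use this for the Kaplan-Meier and log-rank analyses, and for the counts and person-time in the negative binomial model.
- Ask the Aftercare service to supply the coded appointment or consent date, or simply the lag in days. The article does not say that researchers receive it. Report the observed distribution of lags.
- Keep the emergency department visit as time zero in a sensitivity analysis.

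**Cost.** One extra data item and some programming. Events before the landmark leave the main analysis, so it describes the effect from enrolment onward and not the first days after the visit. With an event-free landmark, 75 participants and the same planned ratio, power under the one-sided variant (.0636 vs .16) goes from .805 to .80 (1 day, constant hazard), .757 (7 days, 10% in week 1) or .70 (7 days, 20% in week 1). With .087 vs .219, two-sided without continuity correction, it goes from .857 to .856, .809 or .749. The loss is small when lags are short.

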#### Study duration

The Aftercare intervention commenced receiving referrals on 21 August 2017 from the emergency department of the largest hospital in the region, the Wollongong Hospital, and following the receipt of human research ethics approval, recruitment of study participants commenced on 1 November 2017. The service was rolled out gradually, so the full implementation of the intervention, including referrals from all three participating emergency departments, occurred on 5 March 2018. Data will continue to be collected for 12 months following the recruitment of the 75th intervention group study participant. As such, data collection for the study is forecast to cease by November 2020.

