### Data handling

Primary outcome data of re-presentations to an emergency department and other local health district data on hospital admissions, community mental health and mental health outcomes will be extracted and de-identified by the Centre for Health Research Illawarra Shoalhaven Population (CHRISP), a research centre which performs data linkage through a partnership between the local health district and the University of Wollongong. Deaths attributable to any cause will be obtained from NSW death registration data held by the NSW Centre for Health Record Linkage (CHeReL). The researchers with be provided with the de-identified coded data.

Secondary outcome data (suicide risk factors) will be collected by the Aftercare service prior to the participant attending their initial session with a mental health clinician and again at the time of their final (discharge) session with the clinician. For Aftercare participants who consent for their data to be included in the study, the data will be de-identified and coded within the Aftercare service, prior to being provided to the researchers.

Data transfers and storage will comply with national and state legislation, national ethics principles and University of Wollongong, local health district and the CHRISP data management policies.

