### Limitations

The study groups are non-randomised, hence intervention participants are self-selecting and may therefore constitute a group that is inherently different from controls prior to study commencement, such as having higher motivation to seek treatment or greater levels of psychological mindedness. Controlling such factors will require future randomised controlled trials. The current study is typical of pragmatic trials which test the effectiveness of interventions in a real-world context as opposed to efficacy trials which are in controlled conditions.

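### Two of the three primary hypotheses (re-presentation and death) rest on an unadjusted log-rank test between self-selected groups, so they are open to confounding that the plan adjusts for only in the rate model

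*Protocol article*

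**What the plan says.** The Study design section makes hypotheses 1 to 3 primary. The Data analysis section then assigns the methods.

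- **Hypotheses 1 and 3:** "Presentations to an emergency department with a repeat suicide-related event and for all-cause death will be compared between the two non-randomised groups" by a Kaplan-Meier plot with censoring, and "A log-rank test will compare the Kaplan Meier curves of the two groups".
- **Hypothesis 2:** "A negative binomial regression model will be applied to the data to estimate the effect of the intervention on re-presentation rates", "adjusting for service and person-level characteristics (e.g. facility, age, sex, indigenous status) and censoring".

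On how the groups arise, the Study sample section takes as participants those who consent both to the service and to use of their data. Controls are people who attend a participating department "but either do not receive, or do not accept, a referral to the Aftercare intervention". They must meet the inclusion criteria and are chosen by same month and closest presentation date. Hospital and personal characteristics play no part in the selection.

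The Limitations section states that "intervention participants are self-selecting and may therefore constitute a group that is inherently different from controls prior to study commencement", and leaves control of such differences to future randomised trials.

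**The concern.** The same emergency department records are treated in two ways. The number of re-presentations is compared with adjustment, while the time to the first one is compared without it. Death is also compared without adjustment. This is a stated choice of method, not a detail left to an analysis plan: the article names the test for hypotheses 1 and 3 and places the adjustment elsewhere.

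The log-rank test answers whether two survival curves differ. When one group accepted a service and the other was not offered it or turned it down, a difference can come from the service or from who ended up in each group. The Limitations section is right that motivation and similar traits need randomisation. That argument does not cover facility, age, sex and indigenous status, which the plan already regards as worth adjusting for under hypothesis 2.

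At stake is how two of the three primary results can be read. A small p-value could reflect selection, and a null result could hide a benefit if participants were the higher-risk group.

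**Working it through.** **The plan's own figure.** The Sample size section gives 80% power, α = .05, 12-month proportions .087 and .219, and groups of 75 and 1265, so r = 1265/75 = 16.87. With the two-sided two-proportion formula:

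- Pooled p = (.087 + 16.87 × .219)/17.87 = .2116.
- n′ = [1.96√(17.87 × .2116 × .7884) + 0.842√(16.87 × .087 × .913 + .219 × .781)]² / (16.87 × .132²) = (3.384 + 1.034)²/0.2939 = 66.4.
- Continuity correction: n = (66.4/4) × [1 + √(1 + 2 × 17.87/(66.4 × 16.87 × .132))]² = 16.6 × 2.114² = 74.2, which rounds up to 75.

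The stated 75 is reproduced, although by a two-proportion formula and not a log-rank one. That is a separate matter; the present point does not depend on it.

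**Method by hypothesis.**

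| Primary hypothesis | Method stated | Adjusters stated |
|---|---|---|
| 1, first re-presentation | Kaplan-Meier, log-rank | none |
| 2, re-presentation rate | negative binomial | facility, age, sex, indigenous status (as examples) |
| 3, all-cause death | Kaplan-Meier, log-rank | none |

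**How far a crude comparison could move.** The documents give no baseline imbalance, so every input here is assumed. With no true effect, let a factor multiply risk by g and be present in a share a of participants and b of controls. The crude risk ratio is [1 + a(g − 1)]/[1 + b(g − 1)].

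- g = 3, a = 20%, b = 35%: 1.4/1.7 = 0.82.
- a = 15%: 1.3/1.7 = 0.76. a = 25%: 1.5/1.7 = 0.88.
- Imbalance reversed, a = 35%, b = 20%: 1.7/1.4 = 1.21.
- Weaker factor, g = 1.5, a = 30%, b = 50%: 1.15/1.25 = 0.92.

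**What this does to the test.** Under the Schoenfeld approximation with 75 and 1265 people and no true effect, the chance that a two-sided .05 log-rank test favours the intervention (nominal 2.5%) is:

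| Imbalance mimics a hazard ratio of | 16% control events | 21.9% control events |
|---|---|---|
| 0.9 | 5% | 6% |
| 0.8 | 11% | 14% |
| 0.7 | 22% | 29% |

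A simulation of 1000 runs per scenario, again with no true effect, agrees in kind:

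- **Hazard ratio 3, 30% of participants vs 60% of controls.** The log-rank test rejected in 12.3% of runs, always favouring the intervention, with a median apparent hazard ratio of 0.73. A Cox model adjusted for the factor rejected in 4.3%, with hazard ratio 0.99.
- **Hazard ratio 2, 30% vs 50%.** Log-rank 5.6%, apparent hazard ratio 0.84; adjusted Cox 4.9%, hazard ratio 0.97.
- **Hazard ratio 2, 50% in both groups.** Log-rank 4.5%, apparent hazard ratio 0.96.

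**Cost of adjusting hypothesis 1.** On the plan's rates, expected events are 75 × .087 + 1265 × .219 = 6.5 + 277.0 = 283.6. The implied hazard ratio is ln(.913)/ln(.781) = 0.368, and the intervention share is 75/1340 = .056. Schoenfeld power is Φ(√[283.6 × .056 × .944 × (1 − R²)] × |ln 0.368| − 1.96), where R² is the assumed share of group membership explained by the covariates. It is 97% at R² = 0 and 96%, 93% and 90% at R² = 0.1, 0.2 and 0.3.

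The level depends on the formula and rates. At the same rates, Freedman's version gives 72% without adjustment. At .08 vs .16, Schoenfeld gives 69% without adjustment.

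**Deaths.** The documents give no mortality figure. If 12-month mortality were 1% to 3% (assumption), about 1 to 2 deaths would fall among the 75 participants and 13 to 40 among all 1340.

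**The case against.** The strongest defence has three parts. An adjusted primary analysis of re-presentations is already planned, and it is the one described as estimating the effect. The self-selection is disclosed. The design also removes some differences: controls must meet the inclusion criteria and are aligned on presentation date. All three are correct, and they narrow the point. They do not supply an adjusted test for hypothesis 1 or 3.

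Several stronger readings are tempting but unsupported.

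- **That the comparison is confounded in the intervention's favour.** Nothing in the article says which group carries the higher risk, or by how much.
- **That the adjuster list is deficient because it lacks prior presentations and index type.** The list is given as examples, and the full list is commonly left to an analysis plan. The article does not show how strongly either factor predicts the outcome.
- **That all useful adjusters are already in hand.** The Data handling section says "other local health district data on hospital admissions, community mental health and mental health outcomes will be extracted and de-identified", but states no look-back before the index visit, and does not say that the hospital codes separate attempt from high risk. Availability is firm only for the covariates named for hypothesis 2.
- **That early controls come from departments not yet referring.** The Study duration section describes a staged start, completed in March 2018. A reader might infer such controls, but the Study sample section does not say whether they are drawn before a department began referring.
- **That the trial is sized on both unadjusted tests.** The Sample size section uses one pair of proportions, which the Background reports as re-attempt proportions. Nothing sizes all-cause death by name.

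**Conclusion.** The point holds in limited form. Hypotheses 1 and 3 are tested by a method with no protection against measured differences between groups that the article itself says may differ, while the plan gives hypothesis 2 that protection. The tests are open to confounding; its size and direction cannot be derived from the documents.

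The figures 0.82 and 1.21 illustrate scale under assumed inputs only. The simulated rejection rates run from barely above nominal to more than double it, depending on the imbalance assumed.

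That adjustment is affordable for hypothesis 1 rests on the plan's own event rates, the Schoenfeld formula and an assumed R² of up to 0.3. If the rates are less favourable, power is already short before any adjustment, which is no reason to prefer the crude test.

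**What to change.** Before the outcome data are analysed, amend the Data analysis section as follows.

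- **Hypothesis 1.** Make the inferential analysis a Cox model, or a propensity-weighted Cox model, and state which. Use at least facility, age, sex and indigenous status. Add prior presentations or mental-health contact if the linked extract holds them for the period before the index visit.
- **Calendar time.** Handle it coarsely. Three hospitals by about 24 enrolment months would give some 72 strata for 75 participants.
- **Number of covariates.** Keep it small, or use weighting: intervention events may number only about 5 to 12 (75 × .0636 = 4.8, where .0636 is 16% × .087/.219; 75 × .16 = 12).
- **Hypothesis 3.** Use propensity weighting or a sparse Firth-penalised model.
- **Descriptive results.** Keep the Kaplan-Meier plot and log-rank test, labelled as unadjusted.
- **Limitations.** Retain the statement that motivation and similar unmeasured factors remain uncontrolled.

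The cost is wording, possibly a look-back request to the linkage unit, and some precision: at R² = 0.1 to 0.3 the variance rises by a factor of 1/(1 − R²), that is 1.11 to 1.43. No further participants are needed on the plan's own inputs under the Schoenfeld formula.

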### Measurements

#### Primary outcomes

Hospital emergency department data will be extracted to evaluate the primary outcomes of likelihood of a suicide-related presentation and rate of re-presentations to the three emergency departments as a result of one or more repeat suicide attempt(s) or being at high risk for suicide. Suicide attempt or high risk for suicide will be identified by pre-determined hospital codes. Death registration data will be linked with emergency department data for participants and controls to identify deaths by any cause.

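### The one adjusted primary analysis, the negative binomial model for hypothesis 2, leaves its covariate set open and names only site and demographics; prior suicide-related presentations should be pre-specified, and index type too if the codes allow

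*Protocol article*

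**What the plan says.** All references are to the protocol article.

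- **Model (Data analysis).** "A negative binomial regression model will be applied to the data to estimate the effect of the intervention on re-presentation rates". It allows for unequal follow-up and is described as "adjusting for service and person-level characteristics (e.g. facility, age, sex, indigenous status) and censoring". Hypotheses 1 and 3 are tested by Kaplan-Meier curves and a log-rank test with no covariates, so this is the only adjusted primary comparison.
- **Who the controls are (Study sample).** They are eligible attenders who were not referred to Aftercare or who declined it. They are taken from the same month as participants, choosing those "who had the closest emergency department presentation dates to the participants undertaking the Aftercare intervention and enrolled in the trial". No risk factor enters the selection.
- **What the records hold.** For controls: "Pre-determined hospital codes for suicide attempt or high risk for suicide will identify controls". For the outcome (Primary outcomes): "Suicide attempt or high risk for suicide will be identified by pre-determined hospital codes". Data handling adds that "other local health district data on hospital admissions, community mental health and mental health outcomes will be extracted".
- **What is conceded (Limitations).** Participants are self-selecting and "may therefore constitute a group that is inherently different from controls prior to study commencement". The examples given are motivation to seek treatment and psychological mindedness, and their control is left to future randomised trials.

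**The concern.** In a self-selected comparison with controls chosen only by eligibility and date, the regression is the only tool for making the groups comparable. Hypothesis 2 concerns a recurrent count, and the natural baseline measure is the same count before the index visit. It should be obtainable from the same hospital records that identify controls and count outcomes. Unlike the traits named in Limitations, it is something routine data can supply.

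Referral and acceptance could plausibly depend on how often a person has presented before, and on whether the index visit was an attempt. Both factors plausibly predict further presentations more directly than age, sex or site. If frequent presenters are less often referred or more often decline, they fall into the control group and Aftercare is credited with a difference it did not cause. If they are more often referred, a real benefit could be hidden. An open covariate list in this setting also leaves room to choose terms after the data are seen.

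**Working it through.** **1. The plan's own figure.** The stated 75 and 1265 are reproduced by a two-sided, continuity-corrected comparison of 0.087 with 0.219 at α = .05, 80% power and ratio 1265/75, which gives 75. That calculation uses no covariate and no count model, so it does not bear on this point either way.

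**2. Inputs for the illustration.** The article gives no event rate, dispersion or year-to-year correlation for this population. The only usable counts are those in Background for the control arm of the Danish trial: 22 repeat acts in 64 people, 21.9% with at least one.
- Mean: 22/64 = 0.344 per year.
- Dispersion k from the zero class: (1 + 0.344k)^(−1/k) = 1 − 0.219 = 0.781, so k ≈ 2.54.
- Correlation between a prior-year and a follow-up-year count, if each person's underlying rate is fully stable: kμ/(1 + kμ) = 0.873/1.873 ≈ 0.47. With 60% of the variation shared: 0.6 × 0.47 ≈ 0.28.

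**3. Bias from omitting the prior count.** Gamma-Poisson counts were simulated for 75 versus 1265 people with no true effect. Negative binomial models were fitted with group alone, then with log(1 + prior count) added. The imbalance in underlying rates is assumed. False benefit means a Wald statistic beyond 1.96 in the direction of benefit (nominal 2.5%).

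| Participants' underlying rate | Rate ratio without history | With history | False benefit |
|---|---|---|---|
| × 0.80 | 0.787 | 0.866 | 10.2% → 6.6% |
| × 0.67 | 0.661 | 0.786 | 23.5% → 10.6% |
| × 1.5 | 1.458 | 1.192 | not reported |

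A separate run at × 0.67 gave about 0.65 → 0.77, with false benefit about 22% → 12%. With a less stable rate the shift was smaller, about 0.67 → 0.73.

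Share of bias removed, 1 − ln(adjusted)/ln(unadjusted):
- × 0.80: 1 − ln 0.866/ln 0.787 ≈ 40%
- × 0.67: 1 − ln 0.786/ln 0.661 ≈ 42%
- × 1.5: 1 − ln 1.192/ln 1.458 ≈ 53%
- × 0.67, less stable rate: 1 − ln 0.73/ln 0.67 ≈ 21%

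**4. A binary factor (history yes/no, or index type).** With no true effect, the expected ratio when the factor is omitted is (pT·RR + 1 − pT)/(pC·RR + 1 − pC). Prevalences and RR are assumed.

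| Participants vs controls | RR 1.5 | RR 2 | RR 3 |
|---|---|---|---|
| 30% vs 40% | 0.96 | 0.93 | 0.89 |
| 30% vs 50% | 0.92 | 0.87 | 0.80 |
| 50% vs 30% | 1.09 | 1.15 | 1.25 |
| equal | 1.00 | 1.00 | 1.00 |

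For example, 30% vs 50% at RR 2 gives (0.6 + 0.7)/(1.0 + 0.5) = 1.3/1.5 = 0.87. In a simulation at 30% vs 50% and RR 3 (baseline rate 0.2 per year, dispersion 2), the median ratio was 0.78 without the factor and 0.99 with it; two-sided false rejection was 12% and 5.5%. Adjustment works almost fully here because the simulated factor is itself the confounder, measured without error. A prior count is only a noisy proxy for the underlying rate, hence the partial correction in step 3.

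**5. Precision.** With a fully stable rate, power rises from 79.0% to 82.8% at a rate ratio of 0.397 (.087/.219) and from 53.6% to 59.2% at 0.5. With 60% shared variation the gain at 0.397 is 79.7% to 80.5%. In the binary-factor runs the standard error fell by only 1% to 4%.

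**The case against.** The strongest reply is that the covariate list is introduced as examples. Both factors are person-level characteristics and fit the stated class, and a full protocol or analysis plan that is not shown may name them. This stands against any inference that the plan excludes them. The article shows only that they are neither named nor fixed. It does not dispose of the point: nothing else in the design balances risk, and every example given is site or demographic.

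Other objections also stand:
- The imbalances are assumed. No section says that referral or acceptance depends on history or index type, and shared eligibility rules already narrow severity in both groups. With balanced groups the expected bias is nil.
- The mean and dispersion come from repeat acts in 64 people in another trial, whereas the outcome here also counts high-risk presentations.
- A reader might infer that index type is already on file for everyone. The article never says that the codes separate attempts from high-risk visits. It says codes identify controls and outcomes, while participants enter through clinical assessment and staff referral. No look-back period is stated either.

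Limitations does disclose that the groups may differ. Disclosure is a good reason to leave unmeasured traits to a randomised trial, but a weaker one for a count that linked records should supply.

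**Conclusion.** The point holds as a should-fix. The only adjusted primary comparison has an open covariate set that names facility, age, sex and Indigenous status, and neither prior presentations nor index type appears anywhere as a covariate, stratum or matching factor. Under the assumed imbalances (underlying rates 20% to 33% lower in participants, no true effect), the rate ratio would be about 0.65 to 0.80 without history and 0.77 to 0.88 with it.

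Three stronger readings are tempting and not supported. The article does not show that the bias favours Aftercare: the reverse imbalance gives a spurious ratio above 1. Adjustment would not remove the bias: with the prior count it takes out roughly 20% to 53% on the log scale in these runs, and false benefit stays above its nominal 2.5%. Nor is lost precision the main issue, since the gain is at most about 6 power points and often about 1.

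**What to change.** In Data analysis, replace the open list with a pre-specified set: facility, age, sex, Indigenous status, and the number of coded suicide-related presentations to the three departments in the 12 months before the index visit, entered as log(1 + count). Ask the linkage centre to include that look-back for both groups in the planned extraction. Add index type (attempt versus high risk) if the centre confirms that the codes distinguish the two for participants and controls alike. Report the model without these terms as a sensitivity analysis, and state that residual confounding remains.

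The cost is a sentence or two of text and a modest extension of the extraction, with no new participants, visits or staff. The downsides are one or two more model terms with few events among the 75 participants (about 75 × 0.344 ≈ 26 acts at the control mean used above, fewer if Aftercare works), and prior presentations outside the three hospitals will be missed.
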